**Fig. 4 Fig4:**
[figure not shown]
The Zook classification of fingernail appearance. All split nails, nails with less than two-thirds adherence and very rough nails are considered major deformities. Other deformities are considered minor. The sum of the minor and major variations for each fingertip are used to determine a grade of excellent, very good, fair, or poor for each result

Those patients who are randomised to attend clinic at 4 months and who fail to attend for follow-up will be contacted by telephone and/or e-mail by a research nurse or clinician. These parents will be asked to email a photograph of their child’s repaired fingernail and the contralateral fingernail on the other hand for comparison as per the instructions on the email/letter sent to them. They will also be asked to e-mail their rating of the appearance of their child’s fingernail using the VAS which will be included in the e-mail.

The other half of the patients will be posted a short questionnaire asking about any further treatment sought since their 30-day assessment. A VAS will also be included for the parent and the child to rate the appearance of the fingernail. Parents will also be asked to take a photograph of the nail and send it to a secure email. These images will be collated centrally by the study team in Oxford, anonymised and sent onto independent, blinded assessors. These clinicians will be identified by the study team prior to the start of recruitment. Parents will be asked to send a digital photograph of their child’s fingernail by email to a study email account using the standardised format. An example of a standardised photograph, with the format required, will be sent to the parent for guidance.

### Blinding

NINJA-P is an open study in that those delivering the care will not be blinded to the intervention, nor the patient (and family members) who receives it. A replaced nail can take several weeks to loosen and fall off once a new nail has grown out. The only time that those involved in post-intervention assessment of the nail will be blinded is at the 4-month review. By this time, it is anticipated that all of the replaced nails will have fallen off and been replaced by a new nail. The assessment of the photographs for cosmetic appearance at 4 months will be carried out by a blinded assessor.

### Outcomes and analysis

A single analysis of data will take place once the study has ceased recruiting and the last participant has completed their final assessment. No interim analysis of data is planned nor is a statistical comparison of outcome by treatment group. Descriptive analyses of outcome data will be carried out using appropriate summary measures (e.g. number of events and percentage for binary measures). Outcome data will be grouped according to the allocated intervention irrespective of the actual treatment received. Feasibility measures will be quantified and where appropriate an associated 95 % confidence interval calculated using the Wilson Score Interval method for binary measures. All analyses will be carried out using Stata 13.0 (StataCorp. 2013. Stata: Release 13. Statistical Software. College Station, TX: StataCorp LP.). No imputation of missing data will be carried out.

Withdrawal from the study will result in exclusion of that participant’s data from analysis. If, during the course of surgery, the surgeon has to perform a procedure(s), which was part of the exclusion criteria, this will be recorded on the CRF. This is an extremely unusual event as the vast majority of these procedures (e.g. fracture fixation with a Kirschner wire, need for composite graft or nail bed graft) are predictable pre-operatively. These patients will remain in the trial.

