## Methods/design

### Objectives of the study

NINJA-P is an external pilot study for a large pragmatic, multicentre, randomised, controlled study (NINJA Trial) to assess whether the damaged nail should be replaced or discarded after nail bed repair in children under 16. The primary objective of NINJA-P is to inform the design of the anticipated subsequent main NINJA study specifically in terms of feasibility of recruitment and data collection. In order to achieve this, a range of feasibility measures and clinical outcomes will be collected as listed below.

The feasibility measures are as follows:Number of potentially eligible childrenNumber of patient/parents and guardian’s approached to take part in the studyProportion of children for whom consent was sought which took part in the studyProportion of children who received the allocated treatment and reasons for any non-complianceProportion of participants with a valid response at each follow-up point (for 4-month time point both overall and only by method of follow-up)

The patient-centred outcome measures are as follows:The presence of post-operative complications at 2 weeks and 30 daysThe cosmetic appearance of the nail at 4 monthsThe level of pain experienced by the child at their first dressing change at 2 weeks

The secondary study objectives are to inform the design and conduct of the main NINJA trial as follows:Identify any conflicts or areas of concern for the research pathway compared with the existing standard clinical pathway.Assess suitability of outcome measures for children in this setting.Quantify event proportion and variability data to help inform a sample size calculation for main study.

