### Number of participants

The target sample of size of this study is 60 patients. A study of this size would be sufficient to generate a binary feasibility measure with a 95 % confidence interval width of between 15 and 25 % depending upon the event proportion based upon the Wald interval [14].

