### Intervention 2: discarded nail (group 2)

Group 2 will have the nail plate discarded after the nail bed repair. The washout and debridement and suturing procedures will be the same as described for the first group.

This will be a pragmatic study; hence, the following decisions (whichever arm of the study the patient is in) will be left to the discretion of the surgical team responsible for the patient and recorded appropriately:The type of anaesthetic used (general or local, or both). No stipulation will be made regarding the type of anaesthetic to be used. In this age group, it is normal for the majority of cases to be performed under general anaesthetic as it is uncommon for a young child to be cooperative enough to tolerate a local anaesthetic procedure.Perioperative antibiotics given, if any.Type of tourniquet used.Type of wash used.

The fingertip will be dressed with the same non-adherent dressing in both groups.

Participants in NINJA-P are additionally being randomised to receive one of two follow-up methods for data collection at 4 months (in a manner similar to a SWAT [15]). Half of the patients will be seen in clinic at 4 months to assess the cosmetic appearance of their fingernail. The other half will be followed up remotely using a postal questionnaire, which will also involve asking parents to take photographs of their child’s repaired fingernail and the contralateral unrepaired nail emailing the photographs to a secure address for assessment.

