#### 4 months, clinic and photograph submission

Half of the patients will be seen in clinic at 4 months to assess the cosmetic appearance of their fingernail. The decision as to who will attend the clinic for the 4-month visit and who will just send a photo will have been made at time of randomisation. During the clinic review, a standardised photograph will be taken of the fingernail. This will be taken by a surgeon or clinical research nurse when the child attends clinic using a digital camera. The photograph will include both the affected fingernail and contralateral normal fingernail for comparison. An example of a standardised photograph, with the format required, will be available in the clinic for guidance.

The photograph will be assessed by a different clinician, who is blinded to the intervention the patient received. This clinician will evaluate the cosmetic appearance of the fingernail using a previously validated physician-based outcome tool developed by Zook et al. [10] (Fig. 4). Based on this scoring system, an excellent outcome for the repaired fingernail is defined as one that is identical in appearance to the same finger on the contralateral hand. A very good result exhibits one variation from identical, such as incomplete adherence, nail ridging, split nails or eponychial deformity. A good result exhibits two minor variations from identical. A poor cosmetic result exhibits more than three variations or one major variation from the same fingernail on the contralateral hand. Whilst in clinic, the patient’s parent will also be asked to rate the appearance of their child’s fingernail using a visual analogue scale (VAS). Information about any further treatment sought in between follow-up assessment time points will also be collated.

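### The plan reports 4-month response by randomised follow-up method but states no by-method summary of the appearance scores, so it would not show whether the clinic and remote routes give comparable results or spread

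*Protocol article*

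**What the plan says.** All references are to the protocol article.

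- **Second randomisation.** Under Intervention 2, participants are "additionally being randomised to receive one of two follow-up methods for data collection at 4 months (in a manner similar to a SWAT"). The split is even: "Half of the patients will be seen in clinic at 4 months to assess the cosmetic appearance of their fingernail". The rest are followed up remotely. The Randomisation section confirms two allocations per child.
- **How the data arise.** In the section on the 4-month assessment, the clinic photograph is standardised and taken by staff: "This will be taken by a surgeon or clinical research nurse when the child attends clinic using a digital camera". The parent gives a VAS rating in clinic. In the remote group, "Parents will also be asked to take a photograph of the nail and send it to a secure email", and a posted VAS goes to parent and child. Parents of clinic non-attenders are asked to email a photograph and a VAS rating.
- **Grading.** The Blinding section says that a blinded assessor grades the 4-month photographs.
- **Analysis.** Under Outcomes and analysis: "Outcome data will be grouped according to the allocated intervention irrespective of the actual treatment received". Summaries are descriptive, and no statistical comparison by treatment group is planned.
- **Where method enters the reporting.** Among the feasibility measures (Objectives of the study), the proportion with a valid 4-month response is to be given overall and by follow-up method. No other measure carries that breakdown.
- **Use of the results.** The secondary objectives include assessing the suitability of the outcome measures and "Quantify event proportion and variability data to help inform a sample size calculation for main study". The Background names nail appearance as a co-primary outcome of the main trial.

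**The concern.** Follow-up method changes how an appearance score is produced. For the Zook grade, it changes who takes the picture and under what conditions. For the VAS, it changes the setting and, in the remote group, adds a rating by the child. If the two routes differ in level or spread, a summary by treatment arm mixes them, and its SD or grade distribution describes the mixture rather than either route.

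The choice of follow-up route for the main trial could then rest on response alone. A route with better return but a different or noisier measurement of a co-primary outcome would not be recognised from the summaries the plan states, although the pilot has already randomised the factor needed to look at this.

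**Working it through.** **Inputs from the article.** "The target sample of size of this study is 60 patients"; half are allocated to each follow-up method, so 60/2 = 30 per method. With 1:1 treatment allocation (assumed), each treatment-by-method cell holds about 15. The article gives no SD for appearance, no difference between methods and no target difference for the main trial. These are therefore assumptions, shown over a range.

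**The plan's own precision figure.** Number of participants states a "95 % confidence interval width of between 15 and 25 % depending upon the event proportion based upon the Wald interval". The Wald full width is 2 × 1.96 × √(p(1−p)/60):

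- p = 0.10: 15.2 points
- p = 0.30: 23.2 points
- p = 0.50: 25.3 points

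The stated range reproduces. With 30 children in one method, the same formula gives 21.5 points at p = 0.10 and 35.8 at p = 0.50. A proportion such as the share graded excellent would be known only coarsely within a method.

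**Shift in level between methods (continuous score, equal SDs).** An even mixture of two groups whose means differ by d within-method SDs has variance 1 + d²/4 in units of the within-method variance. Required sample size scales with variance. The last column assumes a 0.5 SD treatment effect and 80% power, where the within-method SD gives 63 per arm.

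| d (assumed) | Variance and N multiplier | SD multiplier | N per arm |
|---|---|---|---|
| 0.2 | 1.01 | 1.005 | 64 |
| 0.5 | 1.0625 | 1.031 | 67 |
| 0.8 | 1.16 | 1.077 | 73 |
| 1.0 | 1.25 | 1.118 | 79 |

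**Difference in spread (no shift).** If the remote SD is r times the clinic SD, the combined variance is (1 + r²)/2 in clinic units.

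- r = 1.25: (1 + 1.5625)/2 = 1.28 times the clinic-only N, and 1.28/1.5625 = 0.82 times the remote-only N.
- r = 1.5: (1 + 2.25)/2 = 1.63 times the clinic-only N, and 1.625/2.25 = 0.72 times the remote-only N.

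A shift alone makes the combined figure too large. Unequal spread can make it too small for the noisier route.

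**What a by-method summary could show.** With complete data on 30 v 30, the 95% CI half-width for the difference in mean VAS is 1.96 × √(2/30) = 0.51 SD. With 20 per method it is 0.62 SD. Power to detect a 0.5 SD difference with 30 v 30 is 49%. That supports description with an interval and gives no ground for a test.

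**The case against.** **The quoted sentence is an intention-to-treat rule.** It sets allocated against received treatment. A reader might infer that outcomes will be shown by treatment and in no other way, but the article does not say so, and nothing in it excludes a further table. This stands. The point is that no by-method summary of appearance is stated, not that one is ruled out.

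**Table layout belongs in an analysis plan that is not shown.** This has force, and such a plan may already contain the table. But the article is not merely silent: it names the one measure to be split by method and says how outcome data are grouped. The first leaves out appearance, which matters given the pilot's own objectives.

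**The routes may differ little.** A reader might take it that half of the appearance results are parents' judgements. For the Zook grade that is not so: photographs are graded blind, and an example of the standard format is provided to clinics and parents alike. The stated difference for the grade lies mainly in image capture. The VAS differs in setting, and the child's rating is named only for the remote group.

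**The variance effect is small beside pilot noise.** Also fair. Assuming normality, a variance estimated from 60 children has a 95% interval of about 0.72 to 1.49 times the estimate, and from 30 about 0.63 to 1.81. A 6% inflation lies well inside either. Zook is moreover an ordered grade, so the SD arithmetic applies to the VAS, and the article does not say that the VAS will be the main trial's appearance measure.

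**The comparison is not free of confounding.** Allocation is randomised, but scores exist only for responders, response may differ by method, and clinic non-attenders move to parent photographs.

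**Conclusion.** The point holds as a gap in the stated reporting. Follow-up method is randomised and changes how appearance is captured. The plan describes response by method but states no such description of the appearance scores, although it must judge outcome suitability and supply variability for a main trial with appearance as co-primary.

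A reader might go further and conclude that the variability passed to the main trial will be wrong, or that it comes from a mixture the main trial would never use. The document supports neither. It gives no difference between methods and no SD, and it does not say that the main trial will use a single follow-up method. The sample-size multipliers of 1.01 to 1.25 for a shift, and about 0.7 to 1.6 for unequal spread, are illustrations that rest on assumed values and a continuous score. No treatment comparison is planned, so no conclusion about treatment is affected.

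The change is worth making because it is cheap and bears directly on two stated objectives.

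**What to change.** Under Outcomes and analysis, add a descriptive summary of Zook grade and parent VAS:

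1. by allocated follow-up method;
2. by route actually obtained (clinic or parent photograph, clinic or home VAS), because clinic non-attenders are asked for parent photographs and emailed ratings.

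Give the difference between allocated methods in mean parent VAS with a 95% CI and no hypothesis test. This does not conflict with the existing statement, which rules out statistical comparison by treatment group. Report the within-method VAS SDs beside the SD for both methods combined, so that those planning the main trial can see which figure fits the route they choose. Treatment-by-method cells of about 15 children need not be a focus.

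The cost is one table from data already due for collection, provided the source of each photograph and VAS is recorded. The drawback is imprecision: about 30 children per method at best, and responders only. The table should say so, and a wide interval should not be read as evidence that the routes agree.

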**Methods/design:**

NINJA-P is a randomised pilot study. The participants are patients below 16 years of age who require surgical repair of the nail bed. Eligible patients will be randomised to receive one of two possible interventions. Group 1 will have the nail replaced after nail bed repair, and group 2 will have the nail discarded. The clinical outcome measures include the presence of post-operative complications at 2 weeks and 30 days, the cosmetic appearance of the nail at 4 months and the level of pain experienced by the child at their first dressings change at 2 weeks. In order to inform the design of the main NINJA trial, the following feasibility data will also be recorded: the number of potentially eligible children and the proportion which agree to take part in the study, the proportion of children who received the allocated treatment and reasons for any non-compliance and the proportion of participants with a valid response at each follow-up point. Neither the patient, family members nor treating physicians will be blinded. A replaced nail can take several weeks to fall off once a new nail has grown out. The cosmetic appearance of the nail at 4 months will be assessed by a blinded assessor.

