### Feasibility data collection

The trial coordinator will collate information from screening logs, change of status forms and from the completion of the follow-up questionnaires throughout the trial. Screening log data will provide information regarding the number of potential patients who were approached, the number who decline and any given reasons for this. Change of status forms will inform the study group of reasons patients withdrew, or were withdrawn by their clinician, from their randomised treatment and/or follow up. The trial database will provide information about the completeness of study forms and attendance at follow-up appointments. The coordinator will also monitor and record feedback from patients/parents and participating clinicians in relation to the follow-up schedule and the content of the CRFs and patient questionnaire.

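### Excluding all data from children who withdraw overstates retention at later visits and discards outcomes already recorded

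*Protocol article*

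**What the plan says.** The Objectives of the study section makes feasibility of recruitment and data collection the primary objective. Its measures include the share of participants who give a valid response at each follow-up point, with the 4-month figure also reported by follow-up method. They also include, in the abstract's words, the "proportion of children who received the allocated treatment and reasons for any non-compliance". A secondary objective is to supply event proportions and variability for the main trial's sample size.

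The Number of participants section says "The target sample of size of this study is 60 patients" and gives the expected precision of a binary feasibility measure as a 95% "confidence interval width of between 15 and 25" percentage points.

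The Feasibility data collection section says that change of status forms will show "reasons patients withdrew, or were withdrawn by their clinician, from their randomised treatment and/or follow up".

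The Outcomes and analysis section covers both clinical outcomes and feasibility measures. It says "Outcome data will be grouped according to the allocated intervention irrespective of the actual treatment received", plans for feasibility measures a 95% "confidence interval calculated using the Wilson Score Interval method for binary measures", rules out imputation, and then states "Withdrawal from the study will result in exclusion of that participant’s data from analysis". Children who turn out at surgery to need a procedure on the exclusion list remain in the trial.

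**The concern.** A child who withdraws before a visit gives no response at that visit. This is one of the events that a retention proportion exists to count. If the child's data leave the analysis, the child leaves the denominator, and the proportion describes only those who stayed. If withdrawal were the only cause of loss, reported retention would always be 100%.

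Two uses of the pilot are affected. First, retention is the natural input to the main trial's allowance for loss to follow-up, and the Discussion lists it among the uncertainties that the pilot is to resolve. Second, the rule reaches back in time. A complication or pain score recorded at 2 weeks, or a complication seen at 30 days, is lost if the child withdraws later, although event proportions and variability are to be taken from these data.

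**Working it through.** **Inputs from the protocol article.** N = 60 (Number of participants); Wald interval for sizing and Wilson interval for analysis; exclusion of withdrawn participants' data (Outcomes and analysis). The article gives no withdrawal or response rate, so every count below other than 60 is an assumption.

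**Step 1: the plan's own figure.** The full width of the 95% Wald interval is 2 × 1.96 × √(p(1 − p)/60). At p = 0.10 or 0.90 this is 15.2 percentage points, and at p = 0.50 it is 25.3. The stated 15 to 25 is reproduced if p is taken to run from 0.10 to 0.90; the article does not state that range.

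**Step 2: effect on retention after withdrawal.** Let w children withdraw before the visit and v of the others respond. Over all randomised, retention is v/N. Under the rule it is v/(N − w). The rule therefore multiplies retention by N/(N − w).

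Main illustration, w = 6 and v = 45:
- All randomised: 45/60 = 75.0% (Wilson 62.8 to 84.2).
- As written: 45/54 = 83.3% (Wilson 71.3 to 91.0).
- Difference: 8.3 points.

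Range over w, with 6 other children missing in each case:

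| Withdrawn | All randomised | As written | Difference |
|---|---|---|---|
| 3 | 51/60 = 85.0% (73.9 to 91.9) | 51/57 = 89.5% (78.9 to 95.1) | 4.5 points |
| 6 | 48/60 = 80.0% (68.2 to 88.2) | 48/54 = 88.9% (77.8 to 94.8) | 8.9 points |
| 12 | 42/60 = 70.0% (57.5 to 80.1) | 42/48 = 87.5% (75.3 to 94.1) | 17.5 points |

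**Step 3: consequence for the main trial.** The inflation factor is 1/retention. In the main illustration it is 1/0.750 = 1.333 over all randomised and 1/0.833 = 1.20 as written. The ratio is 1.20/1.333 = 0.90, so the main trial would recruit 10% too few. In general the ratio is (N − w)/N, so the shortfall equals the share withdrawn: 5% for 3 children, 10% for 6 and 20% for 12. For an assumed need of 500 evaluable children in the table's 6-withdrawal row, 500/0.800 = 625 becomes 500/0.889 = 563 after rounding up.

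**Step 4: visits completed before withdrawal.** Suppose 6 children respond at 2 weeks and withdraw later, and 6 others miss the 2-week visit. Retention at 2 weeks is 54/60 = 90.0%, but as written it is 48/54 = 88.9%. Here the rule understates slightly.

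**Step 5: adherence.** Suppose 6 of 60 do not receive their allocation and 6 withdraw. Over all randomised, adherence is 54/60 = 90.0%. As written it depends on the overlap:
- all 6 withdrawn children were non-adherent: 54/54 = 100%;
- 3 of them were: 51/54 = 94.4%;
- none were: 48/54 = 88.9%.

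The direction is not fixed.

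**Step 6: precision.** With 54 children instead of 60, the Wald width in Step 1 becomes 16.0 to 26.7 points. This loss is minor beside the shift in Step 2.

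**The case against.** The best defence is that the rule concerns a participant's data and was perhaps meant for clinical outcomes only. Withdrawals and their reasons are collected on change of status forms, so retention over all randomised can be recovered at reporting. The pilot is descriptive, it compares no outcomes between treatments, and the article states no progression threshold that retention must meet. In the main illustration, 83.3% also lies inside the 62.8 to 84.2 interval around 75.0%.

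Part of this stands. The bias is avoidable, its size is unknown, and no stated decision turns on it. But recording a withdrawal does not put the child in a denominator, and nothing in the article does so. The outcomes-only reading is not in the text and would still lose events seen before withdrawal. A shift inside the sampling interval is still systematic, and the reported interval would not reflect it.

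Three stronger readings are tempting and are not supported:

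- A reader might infer that adherence is inflated by design. Treatment is a single operation, and randomisation is ideally done just before it, so many children who withdraw later will have received their allocation. Step 5 shows movement in either direction.
- A reader might infer that a child withdrawn by the clinician from the allocated treatment is deleted. The change of status forms cover withdrawal from treatment and/or follow-up, whereas the exclusion rule concerns withdrawal from the study. A child taken off the allocated treatment but still followed is a non-compliance case and stays in.
- A reader might infer a contradiction with grouping by allocation. That sentence settles the group in which a child is summarised, and the withdrawal sentence settles whose data are summarised. Both can be followed at once.

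**Conclusion.** The withdrawal rule is wrong as written and should be fixed. This is more than detail left to an analysis plan, because the article fixes a rule and that rule works against the pilot's primary objective. The firm conclusions are that retention at visits after withdrawal is overstated and that outcomes recorded before withdrawal are lost. Retention at earlier visits may be slightly understated, and adherence may shift either way.

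The size rests on assumed counts: 4.5 to 17.5 points for 3 to 12 withdrawals with 6 others missing, and 8.3 points in the main illustration. The conclusion assumes that the sentence is applied literally to the feasibility measures. It does not show that the pilot's reported figures will be biased, since the records allow the correct proportions to be calculated.

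**What to change.** Replace the sentence in Outcomes and analysis with wording such as:

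> All randomised participants stay in the denominator of the adherence and retention proportions; withdrawal counts as no valid response from that point on. Data collected before withdrawal are kept and summarised by allocated group unless the parent asks for their removal.

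Report the number and timing of withdrawals by treatment allocation and by follow-up allocation.

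The cost is a short change of text and a simple tabulation from forms that are already planned. The downside is that reported retention becomes slightly less favourable.
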